#### Adverse events and protocol deviations

All adverse events defined in the study protocol will be reported as described in Table 3 and compared between the two study groups using logistic regression as described above for secondary outcomes (Table 4). Protocol deviations will be tabulated and reported in the supplementary material.

**Table 4 Tab4:** Secondary outcomes in the total trial cohort

Outcome	Standard care, *N* =	THRIVE, *N* =	Estimate of difference (95% CI)^a^	Adjusted estimate of difference (95% CI)^b^
Number of intubation attempts, *median (IQR)*				
Number of intubation attempts with rescue oxygenation, *median (IQR)*				
Lowest oxygen saturation throughout total intubation period, *median (IQR)*				
Duration of mechanical ventilation, *median (IQR)*				
Ventilation free days, *median (IQR)* ^c^				
Length of ICU stay (days), *median (IQR)* ^c,^ ^d^				
Length of hospital stay (days), *median (IQR)* ^c^				
Minor adverse events				
Bradycardia, not requiring treatment,* n (%)*				
Hypotension, not requiring treatment,* n (%)*				
Main stem bronchial intubation,* n (%)*				
Oesophageal intubation with immediate recognition,* n (%)*				
Emesis without aspiration,* n (%)*				
Epistaxis,* n (%)*				
Dental or lip trauma,* n (%)*				
Major adverse events				
Cardiac arrest with or without return of spontaneous circulation,* n (%)*				
Oesophageal intubation with delayed recognition (> 60 s),* n (%)*				
Emesis with aspiration,* n (%)*				
Hypotension requiring treatment,* n (%)*				
Bradycardia requiring treatment,* n (%)*				
Laryngospasm,* n (%)*				
Malignant hyperthermia,* n (%)*				
Pneumothorax or pneumomediastinum,* n (%)*				
Death during current hospital admission, *n (%)* ^c^				

*SD* standard deviation, *IQR* interquartile range, *CI* confidence interval

^a^Adjusted for study site only

^b^Adjusted for age at randomisation, operator level and study site

^c^Limited to those patients with one enrolment per admission or multiple enrolments receiving the same randomised treatment

^d^Patients with an ICU admission only

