### Sample size

A conservative estimate of the primary outcome of hypoxaemia is set at 16%, following an unpublished 2016 audit of data from the Queensland Children’s Hospital, which we found was comparable to a published report [1]. Assuming a clinically relevant effect size of a 50% reduction in the proportion of desaturation events from 16 to 8%, along with a type I error of 0.025 (adjusting for two primary outcomes using Bonferroni’s correction) and power of 90%, 816 intubation encounters in total are required. Successful first-attempt intubation, the second primary outcome, assumes an absolute increase from 60 to 80%, requiring 258 intubation encounters. Allowing for 15% attrition, the total sample size that will satisfy both primary outcome measures is 960 intubation encounters. An attrition rate of 15% was selected based on the assumption that a proportion of patients enrolled will have a clinical deterioration, or other clinical events, during a high-stress procedure leading to the inability to deliver the intervention or collect the outcome data required for the study.

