### Analysis

#### Outcome definitions

*Intubation attempt* is defined as a single advanced airway manoeuvre beginning with the insertion of the laryngoscope into the child’s mouth and ending when the laryngoscope is removed from the child’s mouth, or where there is a change in operator during the procedure even if the device is not removed.

*Hypoxaemia* is defined as transcutaneous oxygen saturations (SpO_2_) of ≤ 90% or a SpO_2_ saturation difference ≥ 10% for patients with cyanotic congenital heart disease with known substantial right-to-left shunts measured with the bedside monitor and with an accurate quality of the trace during the intubation attempt. Oxygen saturations will continue to be recorded for at least 2 min after the intubation attempt.

A *successful first attempt intubation* is defined as a successful placement of an endotracheal tube at first attempt, without any hypoxemia (SpO_2_ ≤ 90%or saturation difference ≥ 10% for right-to-left shunt). An unsuccessful first attempt intubation is either a successful first attempt intubation associated with hypoxemia, or requirement for more than one intubation attempt.

*Intubation attempt with rescue oxygenation* is defined as the provision of rescue oxygenation (for example, by bag and mask system) following an unsuccessful intubation attempt.

The following are the primary outcomes:

The clinically relevant and patient-centred outcome measures for intubation are hypoxemia and the number of attempts to achieve successful endotracheal intubation, both of which are strongly linked. Therefore, this study has two primary outcomes:Intubation attempt without hypoxaemiaSuccessful first attempt intubation

The following are the secondary outcomes:Number of intubation attemptsNumber of intubation attempts with rescue oxygenationLowest oxygen saturations during each attempt *(intubation attempt as unit of analysis)*

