##### Secondary outcome measures

Binary outcome measures (e.g. occurrence of AE) will be treated in the same manner as the primary outcome; however, no *p*-values will be reported (Table 3). Similar analyses will be undertaken for continuous outcomes: linear regression with adjustment for the treatment group and stratification variables as fixed effects and site and patient as random effects, with reporting of mean difference (unadjusted for stratification variable and adjusted) and 95% CIs. If necessary, quantile regression will replace linear regression in the instance of highly skewed data. Survival outcomes (length of PICU stay, length of hospital stay) will be visually presented using a Kaplan–Meier plot, and a Cox proportional hazard model will be used to assess the differences between the treatment groups with treatment group and stratification variables as fixed effects and site and patient as random effects (i.e. utilising a shared frailty model). The proportionality assumption will be inspected visually using Kaplan–Meier plots and the log–log plot. The hazard ratio and 95% CI will be presented as an estimate of treatment effect. Competing-risk regression will be used to analyse VFDs (competing risk of mortality with duration of ventilation). The lowest oxygen saturation during each intubation encounter will be reported in-text using each encounter as the unit of analysis (and as such incorporating intubation episode as a further random effect into the model). Key assumptions of the models (for logistic regression: specification, goodness-of-fit, absence of multicollinearity and absence of influential observations; for survival analysis: proportionality assumption, goodness-of-fit; for linear regression: specification, distribution of residuals, homoscedasticity, absence of multicollinearity, linearity) will be tested and reported on.

**Table 3 Tab3:** Primary outcomes in the total trial cohort and subgroups as per intention-to-treat analysis

	**Standard care, ** ***N*** ** = **	**THRIVE, = **	**Estimate of difference (95% CI)***	**Adjusted estimate of difference (95% CI)** ^**a**^	***p*** **-value**
**Outcome: hypoxic event** *Oxygen saturations (SpO* _*2*_ *) of* ≤ *90% or a SpO* _*2*_ * saturation difference* ≥ *10% for patients with cyanotic congenital heart disease with known substantial right-to-left shunts*					
**Total trial cohort,** * n (%)*					

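### Number of attempts and rescue-oxygenation attempts are discrete counts summarised by medians; if the skewness fallback is applied at the median, the estimated difference would be essentially zero even at the full planned effect

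*SAP article*

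**What the plan says.** - **Table 4** (under Adverse events and protocol deviations) has the row "Number of intubation attempts, *median (IQR)" and a matching row for attempts with rescue oxygenation. Each row has an unadjusted and an adjusted estimate of difference with a 95% CI.
- **Secondary outcome measures** gives methods for binary, continuous and survival outcomes, and none for counts. Continuous outcomes get a linear model and a mean difference. Where necessary, "quantile regression will replace linear regression in the instance of highly skewed data". No quantile is named, and secondary outcomes carry no p-values.
- **Statistical principles** assigns counts with percentages to discrete variables and keeps the median with IQR for non-normal continuous ones.
- **Sample size**: "Successful first-attempt intubation, the second primary outcome, assumes an absolute increase from 60 to 80%, requiring 258 intubation encounters".
- **Outcome definitions**: first-attempt success "is defined as a successful placement of an endotracheal tube at first attempt, without any hypoxemia". An attempt with rescue oxygenation "is defined as the provision of rescue oxygenation (for example, by bag and mask system) following an unsuccessful intubation attempt".

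**The concern.** Both outcomes are small integer counts with most of their values at the minimum. The median is a poor summary of such data because it stays at the minimum until half the encounters move off it. The plan nevertheless summarises both counts by the median, and its only provision for skewed data leads towards a regression that, at the median, has the same blind spot.

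With no p-values for secondary outcomes, the estimate and its interval are the whole inferential result. A reported difference of 0 could be read as evidence that THRIVE does not change the number of attempts, when the analysis could not have shown a change of the planned size. The Outcome definitions section places the number of attempts beside hypoxaemia as what matters clinically, so a misleading zero here would be noticed.

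**Working it through.** **1. The plan's own sample size.** Inputs from Sample size: two-sided alpha 0.025, power 90%, 1:1 allocation. With pooled variance and no continuity correction, n per arm = [z(0.9875)·√(2p̄(1−p̄)) + z(0.90)·√(p1(1−p1)+p2(1−p2))]² / (p1−p2)².
- 60% v 80%: [2.2414·√0.42 + 1.2816·√0.40]² / 0.04 = 128.04, so 129 per arm and **258** in total, as stated.
- 16% v 8%: [2.2414·√0.2112 + 1.2816·√0.208]² / 0.0064 = 407.3, so 408 per arm and **816** in total, as stated. Then 816/0.85 = **960**, as stated.

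**2. From success rates to counts.** A first-attempt success has exactly one attempt. It also has no rescue attempt, because rescue is defined as following an unsuccessful attempt. So 60% and 80% are lower bounds on the shares with one attempt and with zero rescues. Both exceed 50%, so the medians are 1 v 1 and 0 v 0.

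**3. Sampling error.** With 408 evaluable encounters in an arm, the sample median of attempts exceeds 1 only if 204 or fewer have one attempt.
- Control: P(Bin(408, 0.6) ≤ 204) = **2.7 × 10⁻⁵**. This is an upper bound, since 60% is a lower bound.
- THRIVE at 80%: below 10⁻⁴⁰.
- The same bounds apply to the rescue count.

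**4. Median regression on the attempt count.** Trials of 816 encounters were simulated at 60% v 80%, assuming that later attempts succeed 60% of the time.
- Unadjusted: the treatment coefficient was exactly 0 in 160 of 160 trials.
- Adjusted for age group and operator level: 0 in 120 of 120 trials with no to strong differences between strata. With extreme differences (control success from 26% to 97% across strata) it was 0 in 39 of 40.
- Site and patient random effects were not simulated.

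**5. What the same data contain.** Up to 40% v 20% of encounters need more than one attempt. Under the same assumption the means are about 1 + 0.4/0.6 = 1.67 and 1 + 0.2/0.6 = 1.33, a difference of about a third of an attempt. A comparison of means detected it in over 99% of simulated trials at the 0.05 level.

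**6. Interquartile range.** The upper quartile is 2 when fewer than 75% of encounters have one attempt, and 1 when more do. At 60% v 80% or 70% v 80% the table would read 1 (1–2) v 1 (1–1). In simulation at 70% v 80% the upper quartile differed in 98% of trials. At 78% v 85%, with both arms above 75%, the IQRs differed in only about 9%.

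**7. Sensitivity of an alternative.** The documents give no distribution of attempts, so the single-attempt shares below are assumptions. For more than one attempt v one, at 408 per arm and two-sided 0.05, power ≈ Φ(difference/SE − 1.96).
- 70% v 80%: SE = √[(0.21 + 0.16)/408] = 0.0301; 0.10/0.0301 = 3.32; power about **91%**.
- 78% v 85%: SE = √[(0.1716 + 0.1275)/408] = 0.0271; 0.07/0.0271 = 2.59; power about **73%**.

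Simulated rank tests gave about 91% and 71%. In both scenarios the medians did not differ in any of 2,000 simulated trials.

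**The case against.** Four points on the other side have force.

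- **The fallback is conditional.** The stated default is linear regression, which would show a mean difference; with assumed shares of 70/20/7/3% v 80/14/4/2% for 1/2/3/4 attempts, its power was about 86%. A reader might infer that these outcomes cannot show an effect under the plan. The text does not support that. What remains is that a count with at least 60–80% of its values at the minimum is an obvious candidate for the skewness rule, and Table 4 already presents both counts as skewed.
- **The quantile is inferred.** Only Table 4's median suggests median regression. An upper quantile need not give zero at 60% v 80%.
- **The IQR is informative.** A reader might infer that median (IQR) hides the effect altogether. It does not, as step 6 shows, unless both arms exceed about 75% single-attempt encounters. But the estimate of difference would not reflect what the IQR shows.
- **The impact is limited.** First-attempt success without hypoxaemia is a primary outcome with a logistic model and n (%) display, and it carries much of the same information, though mixed with hypoxaemia. A misleading zero here would not change the trial's main conclusion.

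It can also be argued that the linear and quantile rule covers only continuous outcomes. Then no model at all is stated for these counts, although Table 4 promises estimates of difference for them.

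**Conclusion.** The point holds in conditional form. Table 4's display of two discrete counts departs from the plan's own rule for discrete variables, and no count or ordinal model is named. If the skewness fallback is applied at the median, the estimated difference would be 0 without adjustment, and almost always 0 after adjustment for age group and operator level. That holds for any effect of THRIVE that leaves more than half of the encounters in each arm with one attempt and no rescue.

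The equality of medians rests only on the planned 60% and 80% and on the outcome definitions. The mean difference and the power figures rest on assumed attempt distributions and should be read as a range. The consequence is a possibly misleading report of two secondary outcomes; the primary analysis is not affected. It is worth correcting before the final analysis because the correction is cheap.

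**What to change.** - State that these two outcomes are exempt from the quantile-regression fallback.
- In Table 4, replace median (IQR) with n (%) for 1, 2 and 3 or more attempts, and for any v no rescue oxygenation.
- Analyse the number of attempts with an ordinal (for example proportional-odds) model, or with the logistic model already planned, applied to more than one attempt v one. Analyse any rescue with the planned logistic model. Keep the same stratification terms and the site and patient effects.

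**Cost:** SAP wording and two table rows, with no new data; the plan already provides for declaring changes made after publication. An ordinal model adds a proportional-odds assumption to check, and dichotomising rescue loses some information on repeated rescues.

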## Administrative information

### Trial title and registration

Transnasal humidified rapid insufflation ventilatory exchange in children requiring emergent intubation (Kids THRIVE). This trial is registered in the Australian New Zealand Clinical Trial Registry (ANZCTR12617000147381).

### Protocol versio﻿n

This SAP is based on version 11 of the study protocol. Minor modifications to the original study protocol were reviewed and approved by the HREC and are detailed in the Supplementary Information (Additional file 1).

### SAP version

Version 1 (dated 6 August 2022).

## List of planned Appendix material

- Data and Safety Monitoring Board terms of reference/charter
- Monitoring plan
- Enrolment statistics by month, site, and country
- Results of interim analyses
- Neonatal characteristics of participants enrolled in at a neonatal intensive care unit site or aged < 28 days at time of intubation
- Kaplan–Meier survival curves for length of PICU stay and length of hospital stay
- Forest plot of the treatment effect across subgroups for the primary and secondary outcomes
- Results of per-protocol analysis
- Results of sensitivity analysis
- List of protocol deviations
- List of adverse events
